## 6. Discussion

The efficacy of interventions to reduce anemia can comprise both educational and therapeutic dimensions [2].

Deworming plus nutrition education has been reported to reduce anemia from 82.0% to 55.4%, while increasing the consumption of leafy green vegetables from 44.7% to 60.6% [24]. Furthermore, exclusive educational interventions targeting nutrition improvement, increased the ability of mothers to identify malnutrition (from 15% to 99%), increased exclusive breastfeeding (79% versus 48% in the control group), translated into weight gain (0.86kg versus 0.77kg in the control group), increased vegetable feeding, nutrient-dense foods at lunch (11% difference between the intervention and control groups), dietary requirements for energy, iron and zinc, complementary feeding, and significantly reduced rates of stunting [17,18,19,20,21,35,71].

Exclusive WASH educational interventions, health education on soil-transmitted helminths and schistosomiasis, significantly increased knowledge, reduced both the prevalence of *Ascaris lumbricoides* and *Schistosoma mansoni* and the incidence of hookworms and the intensity of trichuriasis, ascaridiasis and hookworms [25,26]. When deworming is added to WASH education, the prevalence and intensity of STH decrease and school children scored higher than the control on STH knowledge [26,31]. Studies evaluating educational approaches to prevent malaria report improved knowledge regarding breeding sites, bednet use and indoor spraying, increased windows and door net usage and alongside maintaining clean environment practices and leading to a reduced number of reported malaria episodes and the incidence of fever [27,28,39,72].

There are reports of intensity reduction (for *Schistosoma haematobium, Ascaris lumbricoides*, *Trichuris trichiura* and hookworm) and variable cure rates when participants are exposed only to deworming with PZQ or ALB. However, re-infections can occur rapidly [73,74,75,76,77,78,79,80,81,82]. While some authors report that the link between exclusive drug therapy and hemoglobin increase remains inconclusive, others report that exclusively deworming (with ALB and PZQ) may increase mean hemoglobin [83,84]. Additionally, treating malaria has an important impact on anemia reduction [85].

The studies investigating different combinations of those interventions present considerable differences in their designs and methodologies, making it hard to value and compare results [17,18,19,20,21,22,23,24,25,26,27,28,29,31,83,84,86,87,88]. Despite those results, only a few studies have simultaneously implemented a therapeutic plus educational mother-to-child nutrition intervention and compared it with a therapeutic plus educational mother-to-child WASH/Malaria practices [89].

Evaluating the efficacy of educational interventions represents a great challenge, as they are complex, have long causal pathways between the intervention and the outcome, span several intermediate levels and interacting components (in turn susceptible of modifying the effect under measurement and both the internal and external validity of the findings) [90]. One relevant dimension of this complexity is the number of target groups and the number of behaviors required by either those delivering or receiving the interventions for the impact on the outcomes to occur. Educational interventions depend on the knowledge acquired from field technicians, their performance in transmitting that knowledge, skills to conduct community activities and to monitor mother/caretaker practices. Additionally, mothers are expected to be receptive to counselling, gaining awareness of correct parental practices and changing inadequate behaviors and practices. In this study, we postulate that, for a single population, evaluation design, indicators, therapeutic approach and timeline, we will be able to more consistently and realistically describe and compare the effect of: 1) a therapeutic plus educational nutrition; and 2) a therapeutic plus WASH/Malaria interventions on the occurrence of anemia.

Nevertheless, considering the complexity of the design proposed, we can anticipate some difficulties. Randomization may not grant the elimination of all non-measured confounding factors just as the prevalence of several outcomes may be difficult to dilute within the clusters [91]. Additionally, there is also the possibility of poor compliance and differences in the intervention dosage delivered and the amount of response produced. Here, we will distribute nutrition and WASH/Malaria kits during the evaluation moments to prevent low adherence. Furthermore, we are also going to conduct an intensive training/retraining and performance evaluation system for providers, as well as a rotation strategy between technicians and families. The monitoring file of the receiver is expected to collect information on intermediate potential causal steps that will facilitate attributing the observed alterations in outcomes to the intervention, i.e., demonstrating that the intervention was of sufficient magnitude and occurred in a temporal sequence consistent with the hypothesized impact. Additionally, the results from complex cluster-randomized controlled trials, due to the stringencies of the probability statements required, may not be generalizable and further effectivity studies may be needed. Recommendations for overcoming these difficulties include recourse to adequacy and plausibility arguments, combining different types of evidence, in turn limiting the occurrence of bias, confounding factors, and chance [90]. In this study, detailed impact, provision, utilization and coverage indicators will be collected, as described in Table 2.

## 7. Conclusions

Exclusive therapeutic strategies have important results in decreasing prevalence and intensity of infections, however, in a contaminated environment, reinfections rapidly occur. In one hand, WASH/Malaria community-based educational approaches may sustain the achievements of therapeutics by decreasing transmission and, on the other hand, a more accurate evaluation of the effect of community-based educational strategies in adequate IYCF may occur when the influence of infections is removed. The design of this study aims at investigating the effect of 1) exclusive therapeutics (in a focused and context-adapted test-and-treat approach), 2) therapeutics plus educational WASH/Malaria and 3) therapeutics plus educational nutrition strategies. This will allow to clarify key questions that could help improving the control strategies targeting infectious-related and nutrition-related anemia in the country.

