### 1.2. Hypotheses under Study

(1) The nutrition arm assumes that the test-and-treat approach will clear infections and that education in nutrition will improve the knowledge and awareness of caretakers as regards the causes, prevention and treatment of nutritional anemia, which in turn may result in behavioral changes that reduce the prevalence of inadequate breastfeeding and IYCF. This could in turn improve dietary diversity, by increasing the consumption of erythropoietic-rich foods (iron, vitamin B12, vitamin A and folate) and enhancers of iron absorption (vitamin C), and decreasing the inadequate consumption of iron absorption inhibitors (polyphenols, phytates, calcium, etcetera)) [24,35,36], leading ultimately to a decrease in the prevalence of nutritional anemia.

(2) The WASH/malaria arm assumes both that the test-and-treat approach clears infections, and that education in appropriate water, sanitation, personal hygiene and malaria prevention practices improves the knowledge of caretakers regarding the causes and preventive measures against infections, which in turn would lead to behavioral changes, and consequently to reduced prevalence, intensity, incidence and re-infection rates of those diseases [31,37,38,39,40]. Thus, considering that parasitic infections are important causes of anemia within this setting, this intervention would consequently decrease the occurrence of infection-related anemia.

In our study, the intervention in the control group targets the treatment of infections, the intervention in the nutrition arm targets nutritional anemia and nutrition-related causes, and the WASH/malaria intervention focuses on infections and infectious-related anemia. Furthermore, it should be considered that non-malarial infections can also cause anemia through nutritional deficiencies, by causing blunted intestinal villi (which lead to impaired micronutrient absorption) [41]. Thus, by trying to prevent anemia through these 3 possible pathways, we can simultaneously investigate (1) whether combining education in nutrition with a test-and-treat approach could reduce nutritional anemia more than only treating intestinal/urogenital and malaria infections; (2) whether combining education in WASH/Malaria with a test-and-treat approach could reduce nutritional anemia more than only treating intestinal/urogenital and malaria infections; and 3) which of the educational interventions can prevent nutritional anemia the most.

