### 3.2. Randomization

The hamlets will be considered as cluster units. For randomization, the names of the hamlets will be written down on pieces of paper and placed in a bag and then successively removed. The first two papers to be removed will be attributed to the Nutrition arm, the following two to the WASH/Malaria arm and the next pair to the control with this procedure repeated until there are no papers left in the bag. This process will be carried out by the two CISA researchers coordinating the study.

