### 3.6. Recruitment and Promotion of Adherence

To relocate families, field technicians will perform a house-to-house invitation strategy, using Dande’s HDSS household identification system, reference points and family phone numbers. To increase adherence and promote participant retention, the hamlet coordinators and/or traditional authorities will be invited to be present at all phases of the study. Furthermore, incentive kits will be distributed to all children during the follow up moments, namely a nutritional kit (water and yogurt) and a WASH/Malaria kit (soap and lye).

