## Figures and Tables

**Table 1 ijerph-16-00466-t001:** Summary of the treatment given in each arm.

Type of Action	Nutrition Arm:	WASH Arm:	Control Arm
Diagnosis and treatment of: - Malaria (artemether-Lumefantrine 20/120), - Schistosomiasis (Praziquantel) - Intestinal parasites (Albendazol and Tinidazol) Implemented at the baseline and then every 6 months until the end of the study.	Provided	Provided	Provided
Distribution of bednets at the baseline	Provided	Provided	Provided
Distribution of soap and lye at the first and second follow ups	Provided	Provided	Provided
Personalized, home-based counseling of primary caretakers	Provided	Provided	Not provided
Targets within the educational package Each visit will address 2 behaviors of the specified targets topics, moving to the next pair in later visits	(1) Breastfeeding; (2) Complementary feeding *; (3) Weekly adequate food diversity; (4) Appropriate number of meals; (5) Adequate amount of food; (6) Responsible feeding; (7) Disease and alimentation; (8) Hygiene and food safety.	(1) Bednet usage; (2) Reducing mosquito breeding sites (3) Prevention of open sky defecation; (4) Latrine cleaning; (5) Adequate hand washing; (6) Healthy backyard environment; (7) Adequate: water availability, treatment, transportation and storage; (8) Adequate personal hygiene.	Not applicable
Number of counselling visits	6	6	Not applicable
Activities within the community groups	(1) Discussion of nutritional value of foods, the effect of processing and the most common foodborne parasites; (2) Demonstration of fish-and-meat dishes; (3) Demonstration of combinations for breakfast and lunch; (4) Taste and score of recipes; (5) Distribution of illustrative notebook with recipes.	(1) Identification of focus of Soil-transmitted helminth (STH) contamination; (2) Identification of children’s risk behavior in the community; (3) Identification of household indoor resting mosquitos and outdoor breeding sites; (4) Construction of household washing hand mechanisms; (5) Correct montage of bednet; (6) Children hand-washing classes.	Not provided
Number of community group sessions	6	6	Not applicable
Total duration of the follow up	12 months	12 months	12 months

**Table 2 ijerph-16-00466-t002:** Indicators of impact, provision, utilization and coverage being collected in this study.

Impact Evaluation	Process Evaluation		
	Provision * Indicators	Utilization Indicators	Coverage * Indicators

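### No comparison between arms isolates the effect of treatment alone, and the control arm is test-and-treat plus bednets and kits, not treatment only

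*Protocol article*

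**What the plan says.** Section 7 (Conclusions) lists three effects that the trial is to investigate. The first is treatment by itself: "The design of this study aims at investigating the effect of 1) exclusive therapeutics (in a focused and context-adapted test-and-treat approach". The other two are treatment plus WASH/malaria education and treatment plus nutrition education.

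Section 1.2 uses the same picture of the control arm. It says that "the intervention in the control group targets the treatment of infections", and its first two questions ask whether each education package, combined with test-and-treat, reduces nutritional anemia more than treating infections alone. The third question compares the two education packages with each other.

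Table 1 and section 3.6 describe what the arms receive:

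- Diagnosis and treatment is marked as provided in all three arms, "Implemented at the baseline and then every 6 months until the end of the study".
- "Distribution of bednets at the baseline" is marked as provided in all three arms.
- "Distribution of soap and lye at the first and second follow ups" is marked as provided in all three arms.
- Section 3.6 adds that "incentive kits will be distributed to all children during the follow up moments, namely a nutritional kit (water and yogurt) and a WASH/Malaria kit" are handed out. The water and yogurt kit does not appear in Table 1.

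Section 3.2 randomises hamlets to three arms only: pairs go to Nutrition first, then "the following two to the WASH/Malaria arm and the next pair to the control". No arm goes without treatment. Section 5.2 plans comparisons of baseline with follow-up within each sample, and of each intervention arm with control.

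**The concern.** Two statements do not match the design. Section 7 announces an effect of treatment alone, but no arm lacks treatment, so randomisation offers nothing to compare it with. Sections 1.2 and 7 also present control as treatment only, while Table 1 and section 3.6 add bednets, soap, lye, water and yogurt.

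The additions are not neutral extras. The article itself calls the kits nutritional and WASH/malaria kits. Bednet use and hand washing are education targets of the WASH arm in Table 1, and dairy is one of the food groups taught in the nutrition arm (section 3.7).

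What is at stake is the conclusion that the trial may draw. A fall in anemia in the control arm could be reported as the effect of test-and-treat. A null WASH/malaria result, read against section 1.2, would say that education adds nothing to treatment alone. The design supports only the statement that education adds nothing to treatment plus free bednets and supplies. Section 7 wants the results to inform national control strategies, where that difference matters.

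**Working it through.** This is a check of what the design can identify. The article gives no figure to reproduce, and the point does not depend on sample size.

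**Inputs.** From Table 1 and section 3.6, let T = test-and-treat, B = bednets, K = the soap/lye and water/yogurt kits, N = nutrition education, W = WASH/malaria education.

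| Arm | T | B | K | N | W |
|---|---|---|---|---|---|
| Nutrition | yes | yes | yes | yes | no |
| WASH/Malaria | yes | yes | yes | no | yes |
| Control | yes | yes | yes | no | no |

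**Between-arm contrasts.** Three arms give 3 pairs:

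- Nutrition − Control = (T+B+K+N) − (T+B+K) = N
- WASH − Control = (T+B+K+W) − (T+B+K) = W
- Nutrition − WASH = (T+B+K+N) − (T+B+K+W) = N − W

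T has coefficient 1 − 1 = 0 in each, so 0 of 3 contrasts contains the treatment effect. The sums are shorthand and additivity is not needed. If the components interact, N and W are the effects of education where T, B and K are already present, and T is still never varied.

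**Within-arm change in control.** This is the only planned analysis that bears on treatment without education (section 5.2):

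change in control = T + B + K + ageing + season and secular trend + regression to the mean + effects of repeated evaluation.

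It isolates neither T nor treatment in the exclusive sense of section 7.

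**Timing of the shared supplies.** Bednets are present from baseline and so act over the whole 12 months. Kits are given at the follow-up evaluations, which section 4 places at 6 and 12 months. A kit handed out after measurement at 6 months can act only over months 6 to 12, and one handed out after measurement at 12 months cannot affect any outcome. So B is in both the 6-month and the 12-month change, while K enters only the 12-month change and through one distribution.

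**Statements set against the design.**

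| Statement | What the design gives |
|---|---|
| Section 7, first effect: treatment alone | No randomised contrast; an uncontrolled change in an arm that also gets B and K |
| Section 1.2, questions 1 and 2: education against treating infections alone | Education against T+B+K |
| Section 1.2, question 3: one education package against the other | N − W, as stated, with T+B+K common to both |
| Table 1: summary of what each arm is given | Lacks the water and yogurt kit of section 3.6 |

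**The case against.** The strongest reply is that the treatment-alone effect appears in a single sentence of the Conclusions. The formal aim in section 1.1 is to compare two education packages, each combined with test-and-treat. The Discussion names the same two packages, and no stated hypothesis sets treatment against no treatment. Section 5.2 does plan a before-after comparison in each sample, control included, and the article intends to use adequacy and plausibility arguments. On this view section 7 is a loose summary and needs a qualifier rather than deletion. That stands, and the fix allows for it. It does not answer the second part, because section 1.2 is where the hypotheses are set out, and it too describes control as treatment only.

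A second reply is that equal supplies in all arms are a strength: the arms then differ only by education, and Table 1 discloses most of the package. This also stands. Giving supplies to everyone is a legitimate choice; the fault lies in how control is described.

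A reader might go further and infer that the education contrasts are biased, or that free supplies shrink them. The documents do not support either. T, B and K are the same in every arm, so the contrasts estimate education added to that package without bias from it. The direction of any change in the size of the education effect is unknown. Supplies in control might narrow a contrast, but free nets and soap could also enlarge an education effect by making the taught behaviour possible. For yogurt, section 3.7 teaches dairy as a food group while section 1.2 lists calcium among inhibitors of iron absorption. The documents give no figure from which an attenuation could be calculated.

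**Conclusion.** The point holds as a mismatch between what is claimed and what the design can show. One of the three effects named in section 7 is not identified by any of the 3 randomised contrasts, and the control arm's own change cannot stand in for it. Two of the three questions in section 1.2 name a comparator that the trial does not have. One item given to all children is absent from the table that summarises what each arm receives.

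It is not a failure of the formal aim: the education contrasts and the comparison of the two packages remain valid as education on top of a common package. The conclusion rests only on Table 1 and section 3.6 being read as written, with treatment, bednets and both kits going to all three arms. It needs no assumption about the size of any effect.

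**What to change.** 1. In section 7, remove the effect of treatment alone from the list, or label it an uncontrolled before-after description of test-and-treat plus bednets and kits in the control arm.
2. In section 1.2, describe control as test-and-treat plus bednets and kits, and define both education effects as education added to that package. Word any null result accordingly: no demonstrated gain over the package, not over treatment alone.
3. Reconcile Table 1 with section 3.6 on the water and yogurt kit, so that both list the same items for each arm.

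These are changes of wording. They alter neither the design nor the randomised comparisons, nor what any child receives. The cost is a narrower claim: the trial can no longer be presented as measuring what treatment achieves alone, or what education adds to treatment alone.

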## Figures and Tables

**Table 1 ijerph-16-00466-t001:** Summary of the treatment given in each arm.

Type of Action	Nutrition Arm:	WASH Arm:	Control Arm
Diagnosis and treatment of: - Malaria (artemether-Lumefantrine 20/120), - Schistosomiasis (Praziquantel) - Intestinal parasites (Albendazol and Tinidazol) Implemented at the baseline and then every 6 months until the end of the study.	Provided	Provided	Provided
Distribution of bednets at the baseline	Provided	Provided	Provided
Distribution of soap and lye at the first and second follow ups	Provided	Provided	Provided
Personalized, home-based counseling of primary caretakers	Provided	Provided	Not provided
Targets within the educational package Each visit will address 2 behaviors of the specified targets topics, moving to the next pair in later visits	(1) Breastfeeding; (2) Complementary feeding *; (3) Weekly adequate food diversity; (4) Appropriate number of meals; (5) Adequate amount of food; (6) Responsible feeding; (7) Disease and alimentation; (8) Hygiene and food safety.	(1) Bednet usage; (2) Reducing mosquito breeding sites (3) Prevention of open sky defecation; (4) Latrine cleaning; (5) Adequate hand washing; (6) Healthy backyard environment; (7) Adequate: water availability, treatment, transportation and storage; (8) Adequate personal hygiene.	Not applicable
Number of counselling visits	6	6	Not applicable
Activities within the community groups	(1) Discussion of nutritional value of foods, the effect of processing and the most common foodborne parasites; (2) Demonstration of fish-and-meat dishes; (3) Demonstration of combinations for breakfast and lunch; (4) Taste and score of recipes; (5) Distribution of illustrative notebook with recipes.	(1) Identification of focus of Soil-transmitted helminth (STH) contamination; (2) Identification of children’s risk behavior in the community; (3) Identification of household indoor resting mosquitos and outdoor breeding sites; (4) Construction of household washing hand mechanisms; (5) Correct montage of bednet; (6) Children hand-washing classes.	Not provided
Number of community group sessions	6	6	Not applicable
Total duration of the follow up	12 months	12 months	12 months

**Table 2 ijerph-16-00466-t002:** Indicators of impact, provision, utilization and coverage being collected in this study.

Impact Evaluation	Process Evaluation		
	Provision * Indicators	Utilization Indicators	Coverage * Indicators
1. Primary outcomes 1.1 Impact on health - Variation of hemoglobin levels; - Anemia prevalence reduction. 2. Secondary outcomes 2.1 Impact on Health - Iron deficiency anaemia reduction; - Micronutrient deficiencies (iron, folate, vitamins A and B12, zinc and vitamin E serum levels); - Prevalence reduction, intensity, incidence and reinfections rates of STH, *P. falciparum* and *S. haematobium*; - Prevalence reduction of Stunting (height-for-age) and wasting (weight-for-height). 2.2 Impact on Behavior - Exclusive breastfeeding (0–5 months) and continued breastfeeding (12–15 months) [68]; - Increase of Minimum dietary diversity prevalence (6–23 months) [68]; - Increase of Minimum Meal Frequency prevalence [68]; - Increase of iron and vitamin A rich foods consumption; - Reduction of morbidity from diarrhea (reported).	1. Acquired knowledge - Theoretical test scores (evaluation of knowledge); - Practical test scores (evaluation of counseling performance); - Self-counseling efficacy evaluation. 2. Counseling performance - Number of families dropping outs from evaluation moments per technician; - Number of families successfully visited for counseling by each technician; - Number of notified participants present in each community groups per technician; - Number of scheduled visits held successfully per technician.	1. Acquired knowledge of receivers -Theoretical test scores; - Practical test scores (participation in community groups); - Self-evaluation at mother-to-child care. 2. Participatory level of receivers (adherence) - N° of attendances to evaluation moments; - N° of scheduled visits (both in person and by telephone call) held successfully; - N° of scheduled visits that had to be redials due to absence or unavailability; - Mood state of the receiver between visits; - N° of attendances to communitarian group. 3. Household environment evaluation (observation) - N° of household hand washing mechanisms; - N° of communitarian latrines around the house; - Cleaning conditions classification of household latrines (if existent); - Cleaning conditions classification of the backyard; - Presence of pets loose in the yard and stool. 4. Mother-to-children care practices - Children using bednets; - Children sidewalks; - Children with clean nails.	1. Services provided at evaluation moments - N° of hospital-based consultation held for parasite treatment; - N° of domiciliary-based consultation held for parasite treatment; - N° of hospital-based consultation held for sickle-cell follow up; - N° of children referred to the emergencies with severe anemia, severe malnutrition and non-malarial fever who reported to have been followed. 2.Participatory level of receivers (adherence) - Proportion of child-caretaker pair present in all evaluation moments; - Proportion of child-caretaker pair presenting in all counseling moments; - Proportion of caretakers participating in all community groups; - N° of notified child-mother pair failing the hospital-based consultations for parasite treatment or sickle-cell follow up; - N° of child-mother pair failing to picking up the sickle-cell drugs.

* Provision refers to the intervention provided by technicians and utilization refers to the action expected from receivers when provision is delivered.

